## Abstract

**Background:**

The diagnosis of chronic kidney disease (CKD) is based on laboratory results easily extracted from electronic health records; therefore, CKD identification and management is an ideal area for targeted electronic decision support efforts. Early CKD management frequently occurs in primary care settings where primary care providers (PCPs) may not implement all the best practices to prevent CKD-related complications. Few previous studies have employed randomized trials to assess a CKD electronic clinical decision support system (eCDSS) that provided recommendations to PCPs tailored to each patient based on laboratory results.

**Objective:**

The aim of this study was to report the trial design and implementation experience of a CKD eCDSS in primary care.

**Methods:**

This was a 3-arm pragmatic cluster-randomized trial at an academic general internal medicine practice. Eligible patients had 2 previous estimated-glomerular-filtration-rates by serum creatinine (eGFR_Cr_) <60 mL/min/1.73m^2^ at least 90 days apart. Randomization occurred at the PCP level. For patients of PCPs in either of the 2 intervention arms, the research team ordered triple-marker testing (serum creatinine, serum cystatin-c, and urine albumin-creatinine-ratio) at the beginning of the study period, to be completed when acquiring labs for regular clinical care. The eCDSS launched for PCPs and patients in the intervention arms during a regular PCP visit subsequent to completing the triple-marker testing. The eCDSS delivered individualized guidance on cardiovascular risk-reduction, potassium and proteinuria management, and patient education. Patients in the eCDSS+ arm also received a pharmacist phone call to reinforce CKD-related education. The primary clinical outcome is blood pressure change from baseline at 6 months after the end of the trial, and the main secondary outcome is provider awareness of CKD diagnosis. We also collected process, patient-centered, and implementation outcomes.

**Results:**

A multidisciplinary team (primary care internist, nephrologists, pharmacist, and informaticist) designed the eCDSS to integrate into the current clinical workflow. All 81 PCPs contacted agreed to participate and were randomized. Of 995 patients initially eligible by eGFR_Cr_, 413 were excluded per protocol and 58 opted out or withdrew, resulting in 524 patient participants (188 usual care; 165 eCDSS; and 171 eCDSS+). During the 12-month intervention period, 53.0% (178/336) of intervention patient participants completed triple-marker labs. Among these, 138/178 (77.5%) had a PCP appointment after the triple-marker labs resulted; the eCDSS was opened for 73.9% (102/138), with orders or education signed for 81.4% (83/102).

**Conclusions:**

Successful integration of an eCDSS into primary care workflows and high eCDSS utilization rates at eligible visits suggest this tailored electronic approach is feasible and has the potential to improve guideline-concordant CKD care.

**Trial Registration:**

ClinicalTrials.gov NCT02925962; https://clinicaltrials.gov/ct2/show/NCT02925962 (Archived by WebCite at http://www.webcitation.org/78qpx1mjR)

**International Registered Report Identifier (IRRID):**

DERR1-10.2196/14022

## Introduction

### Management of Early Chronic Kidney Disease

Chronic kidney disease (CKD) is common in adults; in the United States, 14% of all adults and nearly half of individuals aged ≥70 years have CKD [1]. CKD is an important predictor of morbidity and cardiovascular mortality [2]. Although most patients with early CKD are seen by primary care providers (PCPs), studies have consistently shown that patients and PCPs remain largely unaware of the patient’s CKD diagnosis until the disease is more advanced [3,4]. Even when early CKD is recognized, PCPs frequently are unaware of the best practices for risk stratification and prevention of CKD-related complications [3]. In particular, both CKD staging and complication risk stratification are greatly improved using a triple marker strategy: urine albumin-creatinine ratio (ACR), estimated glomerular filtration rate (eGFR) based on both serum creatinine levels (eGFR_Cr_) and cystatin-c levels (eGFR_Cys_) [5-9]. Early detection of CKD and risk stratification enable clinicians and patients to take individualized actions that improve outcomes and have the potential to attenuate progression, such as blood pressure management and renin-angiotensin blockade [10-13], statin therapy [13-16], avoidance of nephrotoxic medications [17,18], and glucose management in individuals with diabetes [19-21].

### Approaches to Increase Guideline-Concordant Early Chronic Kidney Disease Management

With the adoption of electronic health records (EHRs), there have been opportunities to implement low-cost interventions to improve patient care. Given that CKD diagnosis is based on laboratory results easily extracted from EHRs, CKD identification and management is an ideal area for targeted electronic efforts [22,23]. Previous studies have shown the feasibility of electronic clinical decision support systems (eCDSS) to improve guideline-concordant care for patients with CKD [24-29]. However, most studies have not been randomized nor have they provided individualized recommendations for patients based on laboratory results. Instead, they have utilized standard reminders or checklists. In addition, concerns about the eCDSS being burdensome or disruptive to workflow have hindered the development and testing of more complex, individualized eCDSS [23,30,31].

Team-based approaches for providing chronic disease management in primary care practice have also been shown to improve patient outcomes [32,33]. For example, blood pressure (BP) control is improved when managed by nonphysician members of the team, including nurses and pharmacists [34-37]. Initial studies have suggested that CKD, like other chronic diseases, may also benefit from a team-based approach [38,39].

### Trial Aims

Given the promise of both eCDSS and team-based care to improve guideline-concordant CKD care in primary care practice, we designed a pragmatic cluster randomized 3-arm trial (usual care; eCDSS; and eCDSS plus pharmacist follow-up). This trial aimed to assess the feasibility and impact of a CKD eCDSS with individualized recommendations and any additional benefit of pharmacist outreach to follow-up compared with usual care. In this paper, we have reported the study design and initial implementation outcomes of this trial.

## Methods

### Overall Design

This was a 3-arm cluster randomized controlled trial with randomization at the provider level. There was 1 usual care control arm and 2 intervention arms. For patients of PCPs in the intervention arms, the research team ordered triple-marker testing (serum creatinine, serum cystatin-c, and urine ACR) at the beginning of the study period, to be completed when the patient visited the lab for regular clinical care. The eCDSS launched for PCPs and patients in the intervention arms during a regular PCP visit subsequent to completing the triple-marker testing. Patients in the eCDSS+ arm also received a pharmacist phone call to reinforce CKD-related education after a PCP visit in which the eCDSS was utilized. We planned for an 18-month trial beginning October 4, 2017, that included a 12-month intervention period and subsequent 6-month follow-up period. This trial was registered on ClinicalTrials.gov (NCT02925962). The University of California San Francisco Human Research Protection Program approved the protocol for this study.

### Setting

This study was conducted at a general internal medicine practice (with 2 locations) at the University of California San Francisco that cares for a diverse population of more than 24,000 adult patients. The PCPs in this practice include faculty attending physicians, resident physicians, and nurse practitioners (NPs). This practice is a certified primary care medical home (PCMH) that follows a team-based approach to care; each of the 10 teams includes 10 to 14 part-time PCPs, 2 medical assistants, a licensed vocational nurse, and administrative staff. Additional personnel of the PCMH include 5 registered nurses, 2 pharmacy technicians, and a clinical pharmacist available 1 day a week. The EHR used within this practice is Epic (EpicCare, Epic Systems).

### Pilot Activities

To optimize the chance of a successful intervention, we worked with a multidisciplinary team (general internist, informatics specialist, and nephrologists) to develop the eCDSS logic. The team focused on areas with the strongest evidence base for CKD management in primary care and developed the logic to apply guideline recommendations in real-time for individual patients. In the first step, patients were classified as either at high risk (eGFR_Cys_ <60 mL/min and/or ACR >30 mcg/mg) or low risk (eGFR_Cys_ >60 mL/min and ACR <30 mcg/mg) for experiencing CKD-related complications [5,17]. After risk stratification, the eCDSS logic focused on 5 domains of CKD care for high-risk patients: (1) cardiovascular risk reduction; (2) potassium management; (3) proteinuria management; (4) appropriateness for nephrology referral; and (5) patient education. For low-risk patients, the logic defaulted to a recommendation for repeat triple-marker testing in 6 months.

We elicited feedback from PCPs in focus group settings during development of the eCDSS and during implementation planning, which is a recommended practice to increase adoption and uptake of eCDSS [23]. Focus group discussions centered on eCDSS messaging and orders, as well as ways to facilitate integration into the usual clinical workflow.

### Eligibility and Selection of Participants

All providers practicing at the general internal medicine practice with a primary care panel were eligible for inclusion and randomization.

Eligible patients were identified using a previously described and validated algorithm [40]. (Patients were considered eligible for inclusion if they were aged 18 to 80 years; had a preferred language of English, Spanish, or Chinese; had at least 2 outpatient eGFR_Cr_=30 to 59 milliliters/minute (mL/min) at least 90 days apart, one of which was within the 12 months before August 14, 2017 (when providers were first contacted for study recruitment); and had a primary care visit in the past 18 months. (see Figure 1 for the Consolidated Standards of Reporting Trial diagram) Participants were automatically excluded (based on EHR data) if they were deceased; diagnosed with end-stage renal disease; engaged with a nephrology clinic with 2 or more visits in the past 12 months; kidney transplant recipients; or diagnosed with dementia. PCPs were then sent a list of potential participants for inclusion and asked to exclude participants for additional criteria that were unreliably captured when extracted from the EHR: current pregnancy, life expectancy <6 months, limited communication ability owing to impaired cognition or severe mental illness, New York Heart Association Class III/IV heart failure, or known ejection fraction <25%. PCPs could also exclude any other participants they felt would be inappropriate for study staff to contact.

**Figure 1 figure1:**
[figure not shown]
Flow diagram of participant selection. Note that 1 clinician who was randomized did not ultimately participate because their only eligible patient opted out. eGFR_Cr_: estimated glomerular filtration rate by serum creatinine; eCDSS: electronic clinical decision support system trial arm; eCDSS+: electronic clinical decision support system and pharmacist follow-up trial arm; N/A: not applicable.

### Recruitment and Consent Process

We recruited PCPs with eligible patients by eGFR_Cr_ by email between August 14, 2017 and September 8, 2017. PCPs were given 2 weeks to either opt-out entirely or exclude individual patients. We then randomized participating PCPs as described below. Participation letters were mailed to eligible intervention arm patients between September 1, 2017 and September 27, 2017, and patients were given 2 weeks to either return an opt-out card or call the study coordinator to opt out. Patients opting out after the study start date of October 4, 2017, were considered withdrawn from the study.

The usual care group PCPs received no additional contact beyond recruitment from the study team, and the usual care patients were never contacted directly by the study team. Usual care PCPs did have access to the same labs and medications to use at their clinical discretion without any recommendations or direction from the study team.

### Randomization and Blinding

We utilized block randomization at the PCP level based on panel size. The study statistician randomized PCP participants to each of the 3 study arms using an automated procedure that accounted for cluster size, to assure balance both in terms of number of patients and number of providers per arm. Eligible patient participants were assigned to study arms based on their PCP’s assignment. The study statistician was blinded to the identification of the PCPs and patients and will be similarly blinded for the analyses.

### Intervention

Before the eCDSS rollout but after randomization, all participating PCPs randomized to an intervention arm were asked to watch an educational video that provided background on guideline-based CKD care, as well as information on what to expect when an enrolled patient participant came in for a visit. PCPs were given an incentive of US $10 and a chocolate bar upon watching the video. Overall, 69.8% (72.0% eCDSS and 67.9% eCDSS+) viewed the video.

Before the eCDSS rollout, between October 5, 2017 and October 12, 2017, one of the study investigators (LK) ordered triple-marker testing for each patient participant from the eCDSS arm (n=169) and each patient participant from the eCDSS+ arm (n=177). We excluded 48 patients who opted out. In total, 10 patients withdrew later.

After the triple-marker testing was ordered, the next time the patient participant visited the lab for their regular clinical care, the triple-marker labs were also collected. We programmed the eCDSS to trigger the first time that the patient participant visited their PCP after all 3 lab results were available. (see Figure 2 for the study workflow) The eCDSS best practice advisory (BPA) appeared above the current medications in the electronic chart (Figures 3 and 4). PCPs could choose to open the BPA by clicking an “accept” button. We also allowed PCPs to view the recommendations by hovering over the BPA before accepting it. For patient participants categorized as low risk, when the PCP accepted the BPA, triple-marker labs with an expected completion date 6 months hence prepopulated were automatically pending for the PCP to sign. For patient participants categorized as high risk, when the PCP accepted the BPA, a SmartSet (EpicCare, Epic Systems) of tailored orders and recommendations appeared (Figure 5). If the PCP did not open the BPA and sign the orders in the SmartSet during the first PCP visit after the triple-marker labs were available, the BPA would trigger at up to 2 additional PCP visits during the study period. The eCDSS did not trigger if the patient participant saw a provider who was not their PCP.

**Figure 2 figure2:**
[figure not shown]
Flow diagram of study workflow for intervention arms. BPA: best practice advisory; PCP: primary care provider.

**Figure 3 figure3:**
[figure not shown]
Electronic clinical decision support system trial arm low-risk best practice advisory. CKD: chronic kidney disease; Cr: serum creatinine; eGFR: estimated glomerular filtration rate.

**Figure 4 figure4:**
[figure not shown]
Electronic clinical decision support system trial arm high-risk best practice advisory. BP: blood pressure; CKD: chronic kidney disease; mg/g: milligrams per grams.

**Figure 5 figure5:**
[figure not shown]
Electronic clinical decision support system trial arm example SmartSet. ACEi/ARB: angiotensin converting enzyme inhibitor / angiotensin II receptor blocker; AVS: after visit summary; CKD: chronic kidney disease; eCDSS: electronic clinical decision support system; CDSS+: electronic clinical decision support system and pharmacist follow-up trial arm; K+: potassium; mg/g: milligrams per grams; NSAID: nonsteroidal anti-inflammatory drug; OTC: over-the-counter;.

In addition to a reminder of BP targets in CKD, the SmartSet for patient participants classified as high risk for progression and/or complications of CKD used real-time EHR lab and medication data to recommend any of the following that applied:

Cardiovascular risk reduction: recommendation for use of statin in all individuals aged ≥50 years not already on a statin, as recommended by Kidney Disease: Improving Global Outcomes (KDIGO) guidelines [17].Potassium management: diet and diuretic recommendations.Proteinuria management: initiation or titration of renin-angiotensin blockade with angiotensin converting enzyme inhibitors (ACEi) or angiotensin II receptor blockers (ARB).Nephrology referral for highest risk participants: highest risk was defined as one of: confirmed eGFR_Cys_ <30 mL/min; potassium >5.5 mEq/L; ACR >300 mcg/mg, systolic blood pressure (SBP) >150 millimeters of mercury (mm Hg) despite 3 agents including a diuretic; >3% risk of five-year progression kidney failure based on Tangri equation [41].Patient education: patient education materials to populate in the after-visit summary (AVS) focused on CKD general information, avoidance of nonsteroidal anti-inflammatory drugs (NSAIDs), and dietary recommendations.

The second intervention arm (eCDSS+) included a pharmacist follow-up visit by telephone. If the SmartSet was signed during the PCP visit, a pharmacist would call the participant within 2 weeks of the visit to reinforce CKD-related teaching and medication changes from the visit as well as complete a comprehensive medication review. Information on the telephone encounter was documented in the EHR and sent to the PCP; any urgent clinical issues identified during the call were highlighted for the PCP as needing their follow-up. Providers in the eCDSS+ group also were encouraged to make a warm handoff to the pharmacist by including anticipatory guidance about the pharmacist phone call within the after-visit summary and distributing a business card with the pharmacist’s photo and phone number for their patient participants at the time of using the SmartSet.

Given that the study physician ordered labs at the start of the intervention period, safety checks were put into place to ensure adequate review of the laboratory results. A nephrologist (LL) from the study team reviewed weekly laboratory results specifically to identify the following: eGFR_Cr_ decline >30% from baseline, ACR ≥1000 mcg/mg, adherence to nephrology referrals, and any discordance >30% between eGFR_Cr_ and eGFR_Cys._ In all of these situations, the nephrologist contacted the PCP to ensure appropriate follow-up. Specifically, in cases of discordance between the 2 types of eGFR levels, the nephrologist advised PCPs to dose medications based on eGFR­_Cys_ when the clinical scenario suggested that eGFR_cr_ may not be accurate.

### Strategies to Encourage Intervention and Behavior Change

Implementation studies have shown that interventions designed with a theoretical basis are more likely to be successful [42,43]. Therefore, we utilized several theory-based strategies to encourage provider uptake of the eCDSS and participant uptake of provider and/or pharmacist recommendations. We classify these strategies using the capability, opportunity, motivation, behavior framework (or COM-B), which asserts that capability, opportunity, and motivation are essential conditions that impact behavior [44,45].

To encourage provider uptake and use of CKD guidelines, we addressed *capability barriers* (such as knowledge about the guidelines or the eCDSS or forgetting to discuss CKD owing to limited bandwidth). During the recruitment phase, we educated eligible PCPs about the prevalence of CKD within their panel by sending a list of their potentially eligible participants along with information about the importance of recognizing and managing CKD early. Shortly before intervention implementation, we sent a training video about the CKD guidelines and the eCDSS to the participating intervention PCPs. The eCDSS itself also served as a prompt to discuss CKD during the visits.

To address PCP *opportunity barriers*, we designed the eCDSS to fit into the physician workflow and to contain all the necessary CKD-related orders and patient education in one easily accessible place during a clinical visit.

To address PCP *motivation barriers*, we provided a small incentive to the participating intervention PCPs who watched the training video. Finally, to enhance use of the BPA, study personnel sent an individual email reminder to the intervention PCP the day before each eligible patient participant visit.

Although the eCDSS itself was a provider-facing intervention, we used strategies to encourage patient participant behavior change. To address *capability barriers* (such as knowledge of CKD or forgetting the provider recommendations), the CDSS SmartSet had CKD-based patient educational handouts in the patient’s preferred language. The pharmacist phone call was also designed to reinforce the knowledge provided at the office visit and *motivate* the patient participant to adhere to medication and avoid NSAIDS.

### Data Collection

For patient participants, the EHR was used to collect baseline data about demographic characteristics (age, sex, race-ethnicity, preferred language, and insurance status); medical co-morbidities (cerebrovascular disease, congestive heart failure, coronary artery disease, diabetes mellitus, hyperlipidemia, and hypertension); current medication prescriptions (statin, ACEi/ARB, and diuretics); previous documentation of CKD on problem list and/or as a visit diagnosis, most recent blood pressure, eGFR­­_Cr,_ eGFR­­_Cys_ (if available), and urine ACR (if available) before enrollment.

Primary outcome data on BP will be extracted from the EHR. Baseline BP was defined as the most recent ambulatory BP measurement before final enrollment on October 4, 2017. All patient participant ambulatory BP measurements were collected during the intervention period and will continue to be collected for the 6 months after the end of the intervention.

Secondary outcomes will be collected primarily using automated EHR data extraction algorithms. The outcomes acquired through data extraction include all secondary outcomes except for provider and patient-centered outcomes, which are collected via surveys. Up to 25 participants in each of the 3 arms were surveyed to assess patient knowledge about CKD and NSAID avoidance. Patient participants in the eCDSS arm were surveyed 2 weeks after a visit in which the SmartSet was utilized; those in the eCDSS+ arm were surveyed 2 weeks after their pharmacist follow-up call, and those in the usual care arm were surveyed 2 weeks after a visit with their PCP during the study period. All participating intervention PCPs will be surveyed about their perception of the feasibility and utility of the eCDSS and pharmacist calls (for CDSS+ providers).

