#### Secondary Outcomes

Our main secondary outcome is PCP awareness of the patient participant’s CKD diagnosis, as measured by inclusion of CKD-related International Statistical Classification of Diseases and Related Health Problems-10th Revision codes on the problem list or as a visit diagnosis. Additional secondary outcomes include process of care, patient-centered, and implementation outcomes.

There are 2 main process of care outcomes: (1) the proportion of patient participants with albuminuria prescribed ACEi/ARB and (2) appropriate use of statins. Appropriate statin use is defined both as the proportion of all patient participants aged ≥50 years prescribed statin therapy and the proportion of participants initiated on statin therapy after study start date.

Patient-centered outcomes include patient knowledge about CKD and NSAID avoidance as measured by patient surveys.

In addition to the effectiveness outcomes described above, the implementation outcomes are described in detail in Textbox 1 using the reach, effectiveness, adoption, implementation, and maintenance (or RE-AIM) framework to highlight measures crucial to successful implementation [47]. In this paper, we report initial implementation results, including all of the Reach outcomes and the first Adoption outcome (PCP SmartSet use).

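### The knowledge survey is triggered by intervention uptake in the two eCDSS arms but by a PCP visit in usual care, so a between-arm difference cannot be read as an effect of assignment

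*Protocol article*

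**What the plan says.** Data Collection sets the survey size: "Up to 25 participants in each of the 3 arms were surveyed to assess patient knowledge about CKD and NSAID avoidance". It then gives three triggers:

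- eCDSS: "Patient participants in the eCDSS arm were surveyed 2 weeks after a visit in which the SmartSet was utilized".
- eCDSS+: "those in the eCDSS+ arm were surveyed 2 weeks after their pharmacist follow-up call".
- Usual care: "those in the usual care arm were surveyed 2 weeks after a visit with their PCP during the study period".

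The Intervention section shows what lies behind the first two. The eCDSS fires only once all three lab results are available and the patient then sees their own PCP. The SmartSet is described for one risk group: "For patient participants categorized as high risk, when the PCP accepted the BPA, a SmartSet (EpicCare, Epic Systems) of tailored orders and recommendations appeared". Low-risk patients instead get repeat labs pended for signature. The pharmacist call has a further condition: "If the SmartSet was signed during the PCP visit, a pharmacist would call the participant within 2 weeks of the visit".

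On the status of the outcome, Secondary Outcomes states: "Patient-centered outcomes include patient knowledge about CKD and NSAID avoidance as measured by patient surveys". Textbox 1 lists both measures as secondary outcomes. The paragraph of Secondary Outcomes that introduces the implementation measures refers back to everything before it, the survey measures included, as effectiveness outcomes.

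**The concern.** Randomisation makes the arms comparable as assigned. It does not make comparable the subsets picked out later by whether the intervention was taken up. An intervention patient enters the survey frame only after completing the labs, seeing their own PCP, and having that PCP act on the advisory; in eCDSS+ the call must also have happened. A usual care patient needs only a PCP visit. Patients who complete labs, attend, and have a responsive PCP may know more (or less) about CKD and NSAIDs whatever their arm.

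At stake is whether a higher knowledge score in the intervention arms could be presented as an effect of the eCDSS or of the pharmacist call. The eCDSS versus eCDSS+ contrast has the same weakness, because eCDSS+ adds the completed-call condition.

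**Working it through.** **1. Reproduce the uptake cascade (Results, Reach and Adoption).** Both intervention arms combined, 165 + 171 = 336:

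- Triple-marker labs completed: 178/336 = 53.0%, as stated.
- PCP visit after the labs: 138/178 = 77.5%, and 138/336 = 41.1%, as stated.
- Advisory opened: 102/138 = 73.9%, as stated.
- Orders signed or education given from the SmartSet: 83/102 = 81.4%, as stated.

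**2. Share of intervention patients who could be surveyed.** SmartSet use is taken as in the last line above.

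- Of all intervention patients: 83/336 = 24.7%, so about 75% could not be surveyed.
- Of those with a PCP visit after the labs: 83/138 = 60.1%.

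These are upper limits. The 83 are not split by risk group, so they may include low-risk patients whose pended labs were signed. The number who then received a pharmacist call is not given. No uptake condition applies to the 188 usual care patients.

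**3. What this could do to a comparison with no true effect.** Let f be the share of usual care respondents who would have reached SmartSet use had they been in an intervention arm. Let d be the knowledge gap, present without any intervention, between such patients and the rest, and p the knowledge rate in the rest.

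- Intervention respondents: p + d.
- Usual care respondents: f(p + d) + (1 − f)p = p + f·d.
- Spurious difference: (1 − f)·d.

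The documents give neither f nor d. Usual care respondents all had a PCP visit. The matching intervention denominator, those with any PCP visit in the period, is not reported, but it lies between 138 and 336. That brackets f between 0.247 and 0.601, if usual care patients would have behaved alike. Values of d are assumed:

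| Assumed d | f = 0.601 | f = 0.247 |
|---|---|---|
| 10 points | 4.0 | 7.5 |
| 20 points | 8.0 | 15.1 |
| 30 points | 12.0 | 22.6 |

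For example, at d = 20: (1 − 0.601) × 20 = 8.0 and (1 − 0.247) × 20 = 15.1. The difference is zero if d = 0 and reverses sign if d is negative.

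**4. Precision.** With 25 per arm and illustrative rates of 60% and 45% (p = 40%, d = 20 points, f = 0.247), the 95% half-width for a difference is 1.96 × √(0.60 × 0.40/25 + 0.45 × 0.55/25) = 1.96 × 0.140 = 0.27, about 27 points. This ignores clustering by PCP.

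**5. Does anything in the article repair the selection?** Analyses applies intention-to-treat to the primary analyses. Its inverse probability weighting is for changes of provider or arm and for differing numbers of assessments or visits, not for selection on SmartSet use or a completed call. No matched usual care subset is described, and Limitations does not mention the point.

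**The case against.** The strongest reply is that the article states no between-arm test or estimate for the survey. Up to 25 patients per arm, in what the authors call a pilot study, is consistent with describing knowledge among people who received the intervention, and the analysis may be set out in a plan not shown here. This stands in part: the article does not claim an intention-to-treat analysis of the survey, and a reader should not infer that it does. But the sampling rule is stated and the outcome is classed with the effectiveness measures. No later analysis plan can restore respondents who were never eligible to be sampled.

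A reader might also infer that the surveyed groups are known to differ in engagement, kidney risk or PCP behaviour. The documents show different entry conditions, not measured differences between respondents. Some of the selection is by PCP action, prompted by an email reminder before each eligible visit, and need not track patient knowledge at all.

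Nor should 15 points be taken as the bias. It is one assumed case; the same gap gives 8 points with the other denominator.

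Finally, surveying each arm 2 weeks after its last arm-specific contact is a defensible anchor. Because the call may come up to 2 weeks after the visit, the eCDSS+ survey can fall about 4 weeks after the visit, against 2 in eCDSS. That is a further difference between the groups, but it does not obviously inflate the eCDSS+ result.

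**Conclusion.** The point holds for interpretation of the survey. The intervention groups are selected on post-randomisation uptake with no usual-care counterpart, and at most 24.7% of intervention patients (60.1% of those with a PCP visit after the labs) could meet the SmartSet condition. A difference in CKD or NSAID knowledge between the arms as surveyed cannot be attributed to assignment.

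The direction and size of any bias cannot be determined from the documents. The 8 to 15 points rest on an assumed pre-existing gap of 20 points and on f lying between the two observed shares. Precision is also low, with a half-width of about 27 points.

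The finding does not reach the primary blood pressure outcome, PCP awareness of CKD, or the outcomes extracted from the EHR. The survey remains usable as a description of patients who met each trigger.

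**What to change.** Report the survey descriptively by arm, with each group labelled by how it was sampled: *among patients whose PCP used the SmartSet* (eCDSS), *who received the pharmacist call* (eCDSS+), and *with a PCP visit* (usual care). Remove the two knowledge measures from the effectiveness outcomes, and make no between-arm test or effectiveness claim from them.

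Data Collection reports these surveys in the past tense, so resampling may no longer be possible. If any remain to be done, sample patients at random in all three arms on one trigger that does not depend on arm or SmartSet use, late enough for the intervention to have acted; a fixed calendar time at the end of the 12-month intervention period is one example. A first PCP visit after study start would not serve, because it would often precede the labs and so the eCDSS itself.

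The cost is rewording and the loss of a small secondary comparison.
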